## Data management

A bespoke data management system was developed by Rilintech Co., Ltd. (Beijing,China) for data storage. The assessment session and data entry are always conducted with at least two assessors to minimise data entry error. Monitoring of study conduct and data collection will be performed by a special committee of the University Clinical Trial Unit on a biannual basis. Recorded data are only accessible by authorised personnel.

## Data analysis

Descriptive statistics will be used to describe the demographic data of each sample group. The normality of each parameter will be checked by histogram and the Kolmogorov-Smirnov test.

Chi-squared tests will be used to assess sample characteristics of gender and types of cerebral infarction.

The pre- and post-intervention differences in gait speed within individuals and between groups will be assessed by paired-samples *t* tests (two-tailed) and one-way analysis of variance (ANOVA), respectively. The comparison of 3-month, 6-month and 1-year follow-ups will be assessed by repeated-measures ANOVA.

A broadly similar approach will be used to analyse the secondary outcome measures of muscle tone, other kinematic parameters of gait, reach forward motion and reach forward and grasp motion. The kinematic parameters of the paretic side will be compared with the nonparetic side at all recording points using paired-samples *t* tests.

The Mann-Whitney *U* test will be used to test the between-group differences for the ordinal data obtained from the functional outcome measures and WHODAS 2.0.

The differences between the two groups during the follow-up phase will be assessed by the Kaplan-Meier test.

There are no planned interim analyses or stopping rules, as the power calculation has accounted for loss to follow-up. All analyses will initially be performed on an intention-to-treat basis.

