**Methods:**

Two hundred and twenty-four acute stroke patients will be recruited from a single centre over a period of 6 years. Participants will be randomly assigned to either conventional therapy or conventional therapy with VR training. Outcomes will be recorded at baseline, post intervention and at 3, 6 and 12 months post intervention. Primary outcome measure is gait speed. Secondary outcome measures include kinematic data of upper and lower limb motion, muscle tone, Action Research Arm Test and Short Orientation Memory Concentration Test.

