## Outcome measures

### Primary outcome measure

Gait speed, assessed by the 10-m Walk Test, is the primary outcome measure.

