### Secondary outcome measures

Secondary outcome measures include 3D motion analysis of upper limb reach forward and reach forward and grasp motions (Figs. 1 and 2) and gait. A breif description of each secondary outcome measure is presented in Table 1. Outcome measures will be recorded at baseline, post intervention and at 3, 6 and 12 months post intervention.

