## Discussion

The VR intervention works on the principle of neuroplasticity [31]. Studies from the past decade suggest that different types of VR can increase gait speed, lower and upper limb functions and kinematic parameters. There are a number of clinical guidelines which recommend active rehabilitation to be commenced within 24 to 48 h of stroke occurrence [32, 33] as the greatest part of the recovery was reported to take place in the first month following stroke [34]. There is some evidence to demonstrate the benefit of an early exercise programme on functional recovery but evidence for early VR intervention is lacking. The majority of the published studies focussed on patients with subacute and chronic stroke [16, 23]. Thus, this study will provide evidence for the use of VR as part of an early intervention programme.

The present study also assesses the medium- to long-term impact of VR interventions for patients with stroke during the acute stage. The Cochrane reviews published in 2011 and 2015 [6, 19] both concluded that it was unknown whether the effects of VR were sustained in the longer term. The review [35] found that only one study [36] out of the 37 included studies had measured the effects of VR on upper limb functions at the 6-month follow-up. Motor capacities evolve most strongly over the first month post stroke [37] and intervention provided at an early stage has better clinical outcomes when compared to intervention provided at a later stage of stroke. Thus, the follow-up data record at 3, 6 and 12 months post intervention will increase the understanding of whether early VR intervention is superior to conventional therapy in the longer term.

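### The primary comparison of gait speed is an unadjusted analysis of change; adjusting for the baseline already recorded is as precise or more so, and the within-arm paired tests do not address the hypothesis

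*Protocol article*

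**What the plan says.** The outcome is fixed: "Gait speed, assessed by the 10-m Walk Test, is the primary outcome measure". A baseline value will exist for it: "Outcomes will be recorded at baseline, post intervention and at 3, 6 and 12 months post intervention".

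The Data analysis section then names the tests: "The pre- and post-intervention differences in gait speed within individuals and between groups will be assessed by paired-samples" (two-sided *t* tests) for the first of these and, for the second, "one-way analysis of variance (ANOVA), respectively". So the paired tests serve the within-person comparison and the one-way ANOVA serves the comparison of arms, both on pre-post differences. No covariate is named here or for the repeated-measures ANOVA of the follow-up visits. The same section applies a broadly similar approach to muscle tone and the kinematic outcomes.

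The Hypotheses section is comparative: it expects more improvement with VR than with conventional therapy. Under Randomisation the article describes 1:1 permuted blocks of 10 and names no stratification factor. Under Sample population, patients enter within one month of a first stroke. Under Control group and Intervention group, both arms receive the routine programme for three weeks and VR is added in one. The Discussion notes: "Motor capacities evolve most strongly over the first month post stroke".

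**The concern.** Two things are at issue.

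**Precision.** Subtracting the baseline assumes that each extra 1 m/s at baseline carries forward as exactly 1 m/s afterwards. If the true slope is lower, change scores over-correct: patients who start slow tend to gain more, and a chance baseline difference between arms leaves a residue in the result. Estimating the slope by ANCOVA removes this at the price of one degree of freedom.

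**Within-arm tests.** The primary hypothesis concerns the difference between arms. A paired test inside one arm asks whether that arm changed at all. In patients recruited within a month of stroke who are all in rehabilitation, change is expected with or without VR. The sentence lists the within-arm and between-arm tests side by side and does not say that only the second bears on efficacy. A contrast of two within-arm p-values is not a comparison of the arms.

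**Working it through.** **Inputs.** From the Sample size section: 112 per arm, 10% missing, 90% power, a target difference of over 0.3 m/s, and 0.16 m/s quoted as the minimum clinically significant difference. Evaluable per arm: 112 × 0.9 = 100.8, taken as 101. Not given: alpha (two-sided 0.05 assumed), the SD, whether that SD is of raw speed or of change, and the baseline-to-post correlation ρ.

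**The plan's own figure.** 112 per arm cannot be reproduced without an SD. Solving the article's formula, σ = δ√(n/2)/(1.960 + 1.282) with n = 100.8:
- δ = 0.30 gives σ ≈ 0.66 m/s
- δ = 0.16 gives σ ≈ 0.35 m/s

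I use 0.35 m/s as the SD of raw speed, with δ = 0.16, for illustration.

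**Variance ratio.** Let the baseline SD be σ and the post-intervention SD be kσ.
- Change score: σ²(1 + k² − 2ρk)
- ANCOVA: σ²k²(1 − ρ²)
- Change score minus ANCOVA: σ²(1 − ρk)², which is never negative

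With k = 1 the ratio of ANCOVA to change score is (1 − ρ²)/[2(1 − ρ)] = (1 + ρ)/2.

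| ρ | ratio, k = 1 | ratio, k = 1.25 |
|---|---|---|
| 0.5 | 0.75/1.00 = 0.75 | 1.172/1.3125 = 0.89 |
| 0.7 | 0.51/0.60 = 0.85 | 0.797/0.8125 = 0.98 |
| 0.8 | 0.36/0.40 = 0.90 | 0.5625/0.5625 = 1.00 |

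**Power** (101 per arm, k = 1, σ = 0.35, δ = 0.16, two-sided 0.05). The residual SD is 0.35√[2(1 − ρ)] for change and 0.35√(1 − ρ²) for ANCOVA.

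| ρ | SD, change | SD, ANCOVA | power, change | power, ANCOVA |
|---|---|---|---|---|
| 0.4 | 0.383 | 0.321 | 84% | 94% |
| 0.5 | 0.350 | 0.303 | 90% | 96% |
| 0.6 | 0.313 | 0.280 | 95% | 98% |
| 0.7 | 0.271 | 0.250 | 98.7% | 99.5% |
| 0.8 | 0.221 | 0.210 | 99.9% | 99.97% |

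Without fixing an SD or a difference: if the change-score analysis had exactly 90% power, ANCOVA with k = 1 would have about 96%, 94% and 93% at ρ = 0.5, 0.7 and 0.8.

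**Chance imbalance.** The baseline difference between arms has standard error 0.35√(2/101) = 0.049 m/s. With k = 1, an imbalance D shifts the change-score estimate by −(1 − ρ)D. For D = 0.049 that is 0.025 m/s at ρ = 0.5 and 0.015 m/s at ρ = 0.7. The shift averages to zero over randomisations.

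**Within-arm tests when VR adds nothing.** A simulation of 4,000 trials (100 per arm, SD 0.35, ρ = 0.7, assumed recovery of 0.16 m/s in both arms, no treatment effect) gave significant paired tests in both arms in 100% of runs. The change-score ANOVA rejected in 5.3% and ANCOVA in 4.8%. With less recovery and more spread (0.10 m/s, SD of change 0.65), each paired test has about 34% power. The chance that exactly one arm is significant is then 2 × 0.337 × 0.663 = 45%, still with no effect.

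**The case against.** The planned comparison is not an error. Under 1:1 randomisation it is unbiased, it held its type I error in the simulation, it uses the baseline (with slope 1), and it matches a hypothesis worded as improvement. All of this stands. A reader might infer that the primary analysis is invalid or biased, or that baseline imbalance is left wholly uncorrected; the documents support neither.

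The gain may also be small. At ρ = 0.7 or 0.8 with the inputs above it is under one percentage point of power. At the article's 0.3 m/s with SD 0.35, both methods are at essentially 100%. A spread that widens during recovery can remove the gain altogether. This stands too, and is why a range is given. Conversely, if the ANOVA sentence is read as applying to post-intervention values, adjustment gains more: the ratio is then 1 − ρ², or 0.51 at ρ = 0.7.

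On the within-arm tests, the article separates their role from the between-group test and nowhere says that efficacy will be judged from them. That is fair; the risk lies in reporting. It is also tempting to say that within-arm change is mainly natural recovery. The documents do not allow that: the change includes conventional therapy and, in one arm, VR, and a patient enrolled late in the first month is treated beyond it.

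Finally, an unseen analysis plan might add a covariate. But the article does not leave the method open; it names an unadjusted ANOVA.

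**Conclusion.** The point holds as a matter of efficiency and of clear inference, not of validity. Adjusting for baseline gait speed is, in large samples, never less precise than the planned analysis. Over ρ from 0.5 to 0.8 the reduction in variance runs from nothing (post SD 1.25 times baseline, ρ = 0.8) to about a quarter (equal SDs, ρ = 0.5). In the illustration, power rises by ten points at ρ = 0.4, six at 0.5, three at 0.6 and less than one at 0.7 and above. All of these rest on assumed values of ρ, the SDs and their ratio.

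The within-arm paired tests cannot isolate VR and do not test the stated hypothesis, whatever those values are.

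A reader might extend the point to the ordinal scales. The article says only that a Mann-Whitney *U* "test will be used to test the between-group differences for the ordinal data obtained from the functional outcome measures and WHODAS 2.0". It does not say whether post or change scores are ranked, so a claim that baseline is ignored there is not supported.

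**What to change.** In the Data analysis section:

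- Make the primary analysis an ANCOVA of post-intervention gait speed on arm with baseline gait speed as covariate, reported as the adjusted difference with its 95% CI.
- Use the same form for the other continuous outcomes.
- Report within-arm change descriptively, without p-values.
- State that efficacy conclusions rest on the between-arm difference only.

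The cost is a change of wording. The baseline is already in the visit schedule, so no visit, measurement or patient is added. The change should be made and dated before any unblinded comparison of the arms.

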## Hypotheses

The primary aim of this study is to test the hypotheses that patients with stroke who receive VR training during the acute stage will have significantly higher improvement in gait speed, lower limb motor functions and upper limb gross and fine motor functions when compared to those who receive conventional therapy. The observed improvements in the VR group will remain significantly higher than the conventional therapy group at 3-, 6- and 12-month follow-up periods. The secondary aim of this study is to assess the changes of the kinematic characteristics of gait and upper limb motions of ‘reach forward’ and ‘reach forward and grasp’ after 3 weeks of VR interventions and at 3-, 6- and 12-month follow-up periods.

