**Fig. 2 Fig2:**
[figure not shown]
**a** Starting position of reach and grasp motion assessed by Vicon. **b** End position of each and grasp motion

**Table 1 Tab1:** Descriptions of the secondary outcome measures

Secondary outcome measures	Descriptions
Action Research Arm Test (ARAT)	The ARAT [41] is a 19-item observational test. It is divided into 4 subtests (grasp, grip, pinch and gross arm movement). Performance on each item is rated on a 4-point ordinal scale ranging from: 0 – can perform no part of test; 1 – performs test partially; 2 – completes test, but takes abnormally long or has great difficulty; 3 – performs test normally
Instrumental Activities of Daily Living (IADL)	The IADL [24] is a functional disability scale which assesses functional level by asking whether a person receives personal help with activities of daily living, such as using the telephone, getting to places outside the house, grocery shopping, preparing meals, doing housework or handyman work, laundry, taking medications and managing finances
Gait analysis	Spatiotemporal gait parameters, joint angles and moment of the lower limbs will be recorded by Vicon Motion Systems, Oxford, UK. Parameters will be recorded at: (1) maximum hip and knee extension during stance phase, (2) maximum flexion at the hip and knee joints during the swing phase, (3) plantarflexion during push-off and (4) dorsiflexion during swing phase of the gait cycle. Spatiotemporal gait parameters of gait speed, cadence, stride length, stride time and step length will be recorded
Upper limb motion analysis	Dynamic changes of shoulder and elbow motions will be measured by Vicon Motion Systems. Parameters recorded during reach forward task (Fig. 1a, b) are: (1) movement time (s), (2) peak velocity (m/s), (3) shoulder amplitude (^o^) and (4) elbow amplitude (^o^)
	Parameters of: (1) movement time (s), (2) peak velocity (m/s), (3) shoulder amplitude (^o^) and (4) elbow amplitude (^o^), (5) supination peak velocity (m/s) and (6) pronation peak velocity (m/s) during reach forward and grasp (Fig. 2a, b)
	Motions for the paretic and nonparetic arms will be recorded and compared
Short Orientation Memory Concentration Test (SOMCT)	The SOMCT [25] is a validated measurement for cognitive impairment. It is a short assessment of cognitive function composed of 6 items

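### The Mann-Whitney U test named for the ordinal functional scales and WHODAS 2.0 is valid but makes no use of the baseline score as a covariate; a baseline-adjusted rank analysis would have more power

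*Protocol article*

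**What the plan says.** All references are to the protocol article.

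- **Data analysis**, on the ordinal outcomes: "The Mann-Whitney *U* test will be used to test the between-group differences for the ordinal data obtained from the functional outcome measures and WHODAS 2.0". This section gives no visit, does not say whether the raw score or the change from baseline is tested, and mentions no covariate. It does not list the functional outcome measures; from Table 1 they would include the ARAT, FMA, BBS and IADL.
- **Data analysis**, on gait speed: pre-post differences are compared within patients and between groups, and for follow-up "The comparison of 3-month, 6-month and 1-year follow-ups will be assessed by repeated-measures ANOVA". This approach is carried over to muscle tone and the kinematic parameters. The ordinal scales are not in that list.
- **Secondary outcome measures**: "Outcome measures will be recorded at baseline, post intervention and at 3, 6 and 12 months post intervention". A baseline score is therefore available for each scale.
- **Table 1**, on the ARAT: "Performance on each item is rated on a 4-point ordinal scale", from 0 to 3 over 19 items, so the total runs from 0 to 57.
- **Hypotheses**: VR patients "will have significantly higher improvement in gait speed, lower limb motor functions and upper limb gross and fine motor functions", and "The observed improvements in the VR group will remain significantly higher than the conventional therapy group at 3-, 6- and 12-month follow-up periods".
- **Primary outcome measure**: gait speed alone. All the ordinal scales are secondary.

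**The concern.** The hypothesis is about improvement, and each patient's starting score is collected. The method named for the ordinal scales takes one number per patient and compares two groups. On later scores, the part of the between-patient spread that baseline would explain stays in the error. On change scores, baseline is used, but by plain subtraction. That treats steps along an ordinal scale as equal, and it adds noise when baseline and later score are only weakly correlated.

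What is at stake is power on the clinical scales, some of which bear on the limb-function part of the primary aim. No power calculation is given for these scales, so it matters that the data already collected are used well.

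**Working it through.** **The plan's own figure.** The only sample size calculation is for gait speed: 112 per group, 10% missing, 90% power, 0.3 m/s. Neither the SD nor alpha is stated, so it cannot be reproduced independently. Taking two-sided alpha 0.05 and 112 × 0.9 = 100.8, rounded up to 101 evaluable per arm, the implied SD is 0.3 × √(101/2) / (1.960 + 1.282) ≈ 0.66 m/s, a standardised difference of about 0.456. It is used here only as a yardstick for the scales.

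**Inputs**

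- Evaluable patients: 101 per arm (from the Sample size section, as above).
- Two-sided alpha 0.05: assumed.
- Effects: 0.456 SD and 0.394 SD, which give a t test 90% and 80% power at 101 per arm: assumed.
- Correlation ρ between baseline and later score: not in the article; 0.3, 0.5 and 0.7 assumed.
- Score range 0 to 57, from the ARAT description.

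**Formula.** Power ≈ Φ( d·√(n·e/2) / √v − 1.960 ), with n = 101, rank-test efficiency e = 0.955 (its large-sample value against the t test for normal data), and relative variance v:

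- later score alone: v = 1
- change score: v = 2(1 − ρ)
- baseline-adjusted: v = 1 − ρ²

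At d = 0.394, d·√(n·e/2) = 0.394 × 7.106 × 0.977 ≈ 2.74. For ρ = 0.5:

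- later score: Φ(2.74 − 1.96) ≈ 0.78
- change: v = 1, so again about 0.78
- adjusted: v = 0.75, Φ(2.74/0.866 − 1.96) ≈ 0.88

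**Simulation.** Correlated normal baseline and later values were rounded and clipped to 0–57, with 4000 runs. Rank ANCOVA regresses the ranked later score on group and ranked baseline. The last two columns are gains in percentage points.

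| Effect (SD) | ρ | Mann-Whitney, later score | Mann-Whitney, change | Rank ANCOVA | Gain over later score | Gain over change |
|---|---|---|---|---|---|---|
| 0.394 | 0.3 | 0.775 | 0.642 | 0.811 | 3.6 | 16.9 |
| 0.394 | 0.5 | 0.775 | 0.763 | 0.864 | 8.9 | 10.1 |
| 0.394 | 0.7 | 0.787 | 0.930 | 0.966 | 17.9 | 3.6 |
| 0.456 | 0.3 | 0.884 | 0.761 | 0.905 | 2.1 | 14.4 |
| 0.456 | 0.5 | 0.885 | 0.881 | 0.948 | 6.3 | 6.7 |
| 0.456 | 0.7 | 0.882 | 0.982 | 0.990 | 10.8 | 0.8 |

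Type I error was 4.6% to 5.7% for all three methods.

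**Independent repeat.** A separate simulation (2000 runs, 0.456 SD) gave, in the same order of methods, 0.886 / 0.730 / 0.908 at ρ = 0.3, 0.876 / 0.871 / 0.949 at 0.5 and 0.885 / 0.970 / 0.984 at 0.7. Type I error was 4.1% to 5.4%. The largest difference from the table is about 3 points (change scores at ρ = 0.3), and the order of the methods is the same. For a smaller effect of 0.30 SD, it gave 0.542 against 0.650 for later score against rank ANCOVA at ρ = 0.5, and 0.535 against 0.796 at ρ = 0.7.

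**Reading the results.** Which Mann-Whitney version is better depends on ρ: later scores do better below 0.5, change scores above. Rank ANCOVA had the highest power in every row, so the point does not depend on which version the sponsor means.

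**The case against.** The strongest reply is that the article is being read too hard, and several parts of that reply stand.

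- A reader might infer that the scales are analysed as unlinked scores with no test of improvement. The text does not say so. It leaves raw or change score open, and a change score links each patient to baseline and tests improvement directly. An article may leave that detail to an analysis plan that is not shown.
- Even on later scores the test is sound. Randomisation makes the expected baselines equal, so a group comparison of later scores addresses whether one group improved more. Chance baseline imbalance is already allowed for in the 5% error rate.
- A reader might also infer that the sustained-benefit hypothesis cannot be tested without a longitudinal model. That does not follow: a between-group comparison at 3, 6 and 12 months addresses it.
- It is tempting to say that three of the four primary-aim domains rest on this test. The article does not map domains to instruments, the scales are all secondary, and kinematics and grip strength also bear on limb function.
- The size of the gain rests on a correlation that the article does not give. At ρ = 0.3 the gain over later scores is only 2 to 4 points.

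What the reply does not remove is that the article chooses a test without a baseline term, and that both ways of applying it had less power than an adjusted analysis of the same data. The Data analysis sentence assigning follow-up group differences to Kaplan-Meier does not help: it names no outcome, and no time-to-event endpoint is defined.

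**Conclusion.** The point stands as one of efficiency, not of bias or validity. For the ordinal scales and WHODAS 2.0, the named test does not adjust for a baseline score that is already collected. At 101 evaluable per arm and effects of 0.394 to 0.456 SD, baseline-adjusted rank analysis gains about 2 to 18 percentage points over Mann-Whitney on later scores and about 1 to 17 over Mann-Whitney on change scores. This assumes two-sided alpha 0.05, ρ between 0.3 and 0.7, and roughly normal scores within a bounded range. The gain over later scores is near the bottom of its range if ρ is low; the gain over change scores is near the bottom if ρ is high. Only single-visit analyses were simulated. The primary outcome is untouched.

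**What to change.** In Data analysis, replace the Mann-Whitney sentence so that the main between-group analysis of the ordinal functional scales and WHODAS 2.0 is a rank ANCOVA: the ranked score at the visit regressed on group and ranked baseline score, at post intervention and at 3, 6 and 12 months. Keep the Mann-Whitney U test as a supportive analysis, and state whether it uses the raw or the change score.

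A longitudinal ordinal model across visits is optional. It was not tested here, and with up to 58 possible ARAT totals its assumptions would need care.

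The change costs wording and a little more analysis work, with no new data or patients. Its one real drawback is that a treatment effect on the rank scale is less directly interpretable, so group medians or another plain summary should be reported beside it.

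### The only method expressly assigned to between-group differences in follow-up is Kaplan-Meier, which fits none of the listed outcomes and leaves the test of sustained benefit unclear

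*Protocol article*

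**What the plan says.** The Hypotheses section sets out, within the paragraph on the primary aim, a claim about durability: "The observed improvements in the VR group will remain significantly higher than the conventional therapy group at 3-, 6- and 12-month follow-up periods".

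The Data analysis section has three sentences that could bear on that claim:

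- For gait speed: "The comparison of 3-month, 6-month and 1-year follow-ups will be assessed by repeated-measures ANOVA". The next paragraph carries this over to other continuous measures: "A broadly similar approach will be used to analyse the secondary outcome measures of muscle tone" and the kinematic parameters.
- For ordinal scores, the Mann-Whitney U test "will be used to test the between-group differences for the ordinal data obtained from the functional outcome measures and WHODAS 2.0".
- With no outcome named: "The differences between the two groups during the follow-up phase will be assessed by the Kaplan-Meier test".

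On the data themselves, the Primary outcome measure section states: "Gait speed, assessed by the 10-m Walk Test, is the primary outcome measure". The Secondary outcome measures section gives the schedule: "Outcome measures will be recorded at baseline, post intervention and at 3, 6 and 12 months post intervention".

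**The concern.** Kaplan-Meier needs, for each patient, a time from a defined origin to a defined event, or to censoring. It yields an estimated curve. A comparison of two such curves needs a further procedure, such as the log-rank test. The article supplies none of these elements, and its outcomes are values read at fixed visits.

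The sentence cannot be set aside as a side analysis, because it is the one place where the article says how the arms will be compared during follow-up. Whether the VR advantage lasts is part of the primary aim, and the Background and Discussion both name the lack of longer-term evidence as a gap that the trial addresses. An analyst following the text would either have to supply an event that the article does not define, or fall back on neighbouring sentences that do not fully say what is compared.

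**Working it through.** No arithmetic decides this point, so the check is a reading of the outcomes and then of the analysis sentences.

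**Step 1. Is any listed outcome an event time?**

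- Gait speed (Primary outcome measure) is continuous.
- Table 1 lists ARAT, IADL, SOMCT, MMSE, Fugl-Meyer, Berg Balance Scale and WHODAS (scores), and grip strength, muscle tone, gait parameters and upper limb kinematics (continuous measurements).
- Some Table 1 items are in units of time: "Parameters recorded during reach forward task (Fig. 1a, b) are: (1) movement time (s), (2) peak velocity (m/s"), and stride time in the gait analysis. These are durations of a task or a stride at one visit, with a value at every visit. They are not times to an event over follow-up.
- Serious adverse events appear only under Safety and adverse event reporting, as a reporting duty and not as an outcome to be compared.
- The Sample size section uses a formula for a difference in means (a standard deviation and a difference in gait speed). It contains no event count and no hazard ratio.

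No listed outcome is an event time, and no event, origin or censoring rule is given anywhere in the article.

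**Step 2. What does each analysis sentence settle?**

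| Method | Outcome | Compares arms? | Follow-up visits? | Fits the outcome? |
|---|---|---|---|---|
| Repeated-measures ANOVA | Gait speed; by extension muscle tone and kinematics | Not stated | 3, 6, 12 months | Yes |
| Mann-Whitney U | Ordinal scores | Yes | Not stated | Yes |
| Kaplan-Meier | Not named | Yes | Follow-up phase as a whole | No |

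The hypothesis needs a yes in each of the last three columns. No row has one. The only row that expressly joins the arms to the follow-up phase is the one whose method does not fit.

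**Step 3. What would the ANOVA give if group were a factor?** Write d3, d6 and d12 for the VR-minus-control differences at the three visits. The group main effect concerns their average, (d3 + d6 + d12)/3. The group-by-time term concerns whether d3 = d6 = d12. The hypothesis concerns d3, d6 and d12 one by one. Contrasts within the same model give these directly, so the ANOVA can serve once group and the contrasts are stated.

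**Step 4. Does any figure in the plan depend on the sentence?** No. The stated size is 112 per group for 90% power at a difference of 0.3 m/s with 10% missing. Neither the standard deviation nor the type I error is given a value, so the figure can be neither confirmed nor refuted. Assuming two-sided 0.05:

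- Evaluable per group: 112 × 0.9 = 100.8, about 101.
- Implied SD = 0.3 / [(1.960 + 1.282) × √(2/101)] = 0.3 / 0.456 ≈ 0.66 m/s.

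This is a calculation on means throughout. Deleting the Kaplan-Meier sentence changes nothing in it.

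**The case against.** The best case for the plan is that follow-up is already covered. Repeated-measures ANOVA is named for the 3-, 6- and 12-month data, and in a two-arm trial one would expect group as the between-subject factor. Mann-Whitney U is named for between-group comparison of ordinal scores and can be run at each visit. A journal article need not list model terms and contrasts; the full protocol or analysis plan may do so, and may also define an event in advance. The Kaplan-Meier phrase may be loose wording for a log-rank test on some such event.

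Much of this stands. A reader might infer that the sustained-benefit hypothesis has no valid test at all. The article does not support that, because the ANOVA and Mann-Whitney sentences can both be made to answer it. Nor is the ANOVA sentence wrong for leaving out contrasts; that detail can sit elsewhere. A reader might also infer that an event would be chosen after the data are seen, or try to put a figure on the information lost by dichotomising gait speed. The article proposes no cut-off and says nothing about when one would be set, so neither inference is supported.

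What the objection does not remove is the sentence itself. The article does not stay silent on how the arms are compared in follow-up. It names a method, and that method does not fit any outcome listed. Reading it as a log-rank test does not help, because that test needs the same missing event. It also leaves two methods attached to the follow-up data without saying which decides.

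**Conclusion.** The point holds as a wrong method stated in the text, together with ambiguity about what replaces it. It affects the between-group comparison at 3, 6 and 12 months, which belongs to the primary aim, so it should be corrected before analysis. It does not affect the post-intervention comparison of gait speed or the sample size, and no numerical loss can be attached to it.

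The conclusion rests on the outcome list in the article being complete. If the full protocol contains an event-time outcome that the article omits, the fault shrinks to a missing definition, but the between-group follow-up test for gait speed would still need to be stated.

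**What to change.** Limit the change to the follow-up analyses.

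1. Delete the Kaplan-Meier sentence. If an event-time outcome is meant, name it and define its event, time origin and censoring rule in advance, together with the test that compares the arms.
2. State that gait speed and the other continuous outcomes are compared between arms in follow-up by a repeated-measures model, for example a mixed model, with arm, visit, arm-by-visit and the baseline value. Report the VR-minus-control difference with a 95% confidence interval at 3, 6 and 12 months, and name these contrasts as the test of sustained benefit.
3. Keep Mann-Whitney U for the ordinal scores, and say that it is applied at each follow-up visit.

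The post-intervention ANOVA need not change on account of this point. The cost is a few sentences of analysis text. No visit, measurement or patient is added, and the sample size stays as it is.
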